#### Primary Analysis

Analysis of the primary outcome will follow the intention-to-treat principle. It will be based on the full analysis set. To test whether the study intervention differs from standard care 30 days after randomization, the Pearson's χ^2^-test without Yates's correction will be applied. Threshold for rejecting the null hypothesis will be α = 5%. The estimated absolute difference between study arms will be reported alongside its 95% confidence interval.

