### Randomization

Participants will be randomly 1:1 assigned to either the targeted-sodium-correction group or the standard treatment group. Randomization will be performed by the online database system SecuTrial®, stratified by study site and using permuted block of random sizes. The allocation sequence will be implemented by the study data manager of the clinical trial unit Basel, Switzerland. Randomization will be done directly after inclusion of each patient in the online database system.

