#### Secondary Analysis

Each of the components of the primary outcome, death and rehospitalization, will be analyzed separately as described for the primary outcome. Time to death and rehospitalization after 30 days and 1 year will be analyzed by fitting Cox proportional hazards regression models with trial arm as explanatory variable. Hazard ratios including their confidence intervals will be reported. Patients will be censored on their last known follow-up. To illustrate the course of deaths and re-hospitalizations in the two treatment arms, a Kaplan-Meier Curve will be presented.

Length of hospital stay will be calculated in days considering index and each rehospitalization separately and by the sum of all hospital stays. Standard summary statistics for numerical data will be performed. If distribution of data allows, significant differences of mean of length of hospital stay between arms will be assessed with a *t*-test (two-sided α = 5%). If distribution is skewed, data will be transformed or other models selected.

The secondary outcomes (falls, fractures, course of hyponatremia, recurrence of hyponatremia, severe symptomatic hyponatremia, overcorrection of hyponatremia) will be analyzed as described for the primary outcome. To account for multiple occurrences of falls, fractures, and recurrence of hyponatremia after 1 year, we will apply a Poisson model.

Diagnostic performance of biomarkers will be assessed by calculating sensitivity, specificity and accuracy as well as best cut-offs. Gold standard is the correct diagnosis of etiology of hyponatremia, which is expert opinion based on biochemistry results and treatment response.

Analyses of differences of quality of life score and of executive functioning score between arms will be performed also considering grade of hyponatremia and its correction. Multivariate linear models will be used to explore possible associations.

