### Subgroup Analyses

We are interested in whether the treatment effect, i.e., the difference between the two treatment arms, on the primary outcome and its components varies between the following patient subgroups: sex (female and male), age (<70 and ≥ 70 years), severity of hyponatremia (mild-moderate: 120–130 mmol/l and severe: <120 mmol/l), underlying disease (stroke, heart failure, SIAD, hepatic impairment, chronic kidney disease, malignancy, surgical diagnosis) as well as the main treatment used (fluid restriction, diuretics, infusion, urea, vaptans). To this end, we will fit logistic regression models, including treatment arm, subgroup and the interaction term as explanatory variables. Significance for interaction is defined by α = 5%. If a significant interaction effect results, the treatment effect will be calculated for the respective outcome and subgroups separately.

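### Randomisation is stratified by study site but the stated primary test ignores site: the test is valid, slightly conservative, and can be improved at almost no cost

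*Protocol article*

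**What the plan says.** - **Randomization:** allocation is 1:1 and "stratified by study site and using permuted block of random sizes".
- **Primary Analysis:** for the 30-day composite of death or rehospitalisation, the Pearson chi-square "test without Yates's correction will be applied". The section adds: "The estimated absolute difference between study arms will be reported alongside its 95% confidence interval". Site is not mentioned for either.
- **Secondary Analysis:** the components, "death and rehospitalization, will be analyzed separately as described for the primary outcome". Falls, fractures, recurrence, overcorrection and the other binary outcomes follow the same method. Time to event uses "Cox proportional hazards regression models with trial arm as explanatory variable", with no mention of site.
- **Subgroup Analyses:** logistic models "including treatment arm, subgroup and the interaction term as explanatory variables".
- **Determination of Sample Size:** the calculation is for the same unadjusted Pearson test, with 23% against 18%, two-sided 5% and 80% power.

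No analysis in the article uses site as a stratum, covariate or random effect, and no reason is given for leaving it out.

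**The concern.** Permuted blocks within site keep the arms balanced on site. If sites have different event rates, that balance reduces the true sampling variance of the risk difference. The pooled chi-square and the usual interval for a difference of two proportions use the total binomial variance, which still contains the between-site part. The standard error is then larger than the design warrants, so the test rejects a true null less often than 5% and the interval is wider than it need be.

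Site differences are plausible here. The Ethics Statement lists nine centres in five countries, and the Discussion says that non-academic hospitals take part. Rehospitalisation, the larger component in the planning data (18.5%, against 6.4% for death), may well depend on local admission and discharge practice. The plan has almost no spare power, so even a small amount of recoverable precision is worth having if it costs little.

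**Working it through.** **1. The plan's own figure.** The inputs from Determination of Sample Size are 0.23 and 0.18 (difference 0.05), mean 0.205, z-values 1.960 and 0.842.

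n per arm = [1.960 × √(2 × 0.205 × 0.795) + 0.842 × √(0.23 × 0.77 + 0.18 × 0.82)]² / 0.05² = 1,022.2, rounded up to 1,023. That is 2,046 evaluable patients against the stated 2,050. Dropout: 2,050 / 0.9 = 2,278, as stated. Power at 1,025 per arm is 80.1%. The calculation reproduces, and planning and analysis agree on an unadjusted test.

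**2. Simulation of the effect of ignoring site.** Taken from the documents: nine sites, 2,050 evaluable patients, rates of 23% and 18%. Assumed, because the documents do not give them: site shares from 4% to 25% of patients, equal arms within each site, and normally spread site effects on the log-odds scale. There were 100,000 trials per scenario, so the Monte Carlo standard error is about 0.07 points for type I error, √(0.05 × 0.95 / 100,000), and 0.13 points for power. Both tests were applied to the same simulated data.

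| Site log-odds SD | Control rates across sites | Type I error, Pearson | Type I error, stratified | Power, Pearson | Power, stratified |
|---|---|---|---|---|---|
| 0 | 23% | 5.1% | 5.1% | 80.0% | 80.1% |
| 0.2 | 18–30% | 4.9% | 5.0% | 80.4% | 80.6% |
| 0.3 | 15–33% | 4.8% | 5.0% | 80.4% | 80.9% |
| 0.5 | 11–41% | 4.4% | 5.0% | 80.8% | 82.0% |
| 0.8 (extreme) | 6–51% | 3.7% | 5.0% | 81.4% | 84.4% |

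Stratified means the Cochran-Mantel-Haenszel test by site. The Pearson test also gains power as sites diverge, because the arms are balanced within site. The loss is therefore the gap between the two power columns, not the distance from 80.1%.

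**3. The interval.** Under the null, coverage of the unadjusted 95% interval was 94.9% at SD 0, 95.6% at SD 0.5 and 96.3% at SD 0.8. With equal arms within site, the Mantel-Haenszel risk difference equals the pooled difference, so only the standard error changes. Under the planned effect, the ratio of stratified to unadjusted variance was 0.9461 at SD 0.5 and 0.9922 at SD 0. The second value reflects a small downward bias in the stratified estimate. Net of that, 0.9461 / 0.9922 = 0.9535, and √0.9535 = 0.976, so the interval is about 2.4% narrower. Simulated coverage of the stratified interval was 94.7% to 94.9%.

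**4. Cross-check by formula at SD 0.5.** Under the null the net variance ratio is 0.9427 / 0.9922 = 0.950, so type I error = 2 × [1 − Φ(1.960 / √0.950)] = 4.4%. Under the planned effect the Pearson statistic has mean 0.05 / √(2 × 0.205 × 0.795 / 1,025) = 2.804. Its SD is 0.998 × 0.976 = 0.975, where 0.998 = √(0.3247 / 0.32595), the ratio of unpooled to pooled variance. Power is Φ[(2.804 − 1.960) / 0.975] = 80.7%. Stratified, it is Φ[(2.804 / 0.976 − 1.960) / 0.998] = 81.9%. Both agree with the simulation.

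**The case against.** The strongest reply is that nothing here is an error. The trial was sized for a Pearson test and will be analysed with one, so the promised 80% power is delivered. The test is simple, valid and errs on the safe side. The loss depends on between-site variation that the documents do not report, and it is nil if there is none. With 750 participants included and treatment open, changing a published primary analysis needs justification, and a site-stratified sensitivity analysis might be thought enough. All of this is accurate, and it limits how strongly the point can be put. It does not show that leaving site out has any benefit. At SD 0 the stratified test loses no power, it holds its type I error in every scenario, and it keeps both the reported measure and the sample size.

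Three stronger readings are tempting but not supported:

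- **That the primary result would be biased or the error rate inflated.** The opposite holds: type I error is at or below the nominal level, within simulation error.
- **That adjustment would buy several points of power.** A reader might reach this by supposing that site, age and baseline sodium together explain a sizeable share of outcome variance. The documents give no such share. Age and sodium were not stratification factors, so a gain from them is not owed to the randomisation. Such a gain is possible but cannot be quantified here.
- **That the Cox models exclude site.** The article names arm as explanatory variable and does not say that it is the only term. Stratifying the baseline hazard by site adds no explanatory variable and is compatible with the wording. A condensed article may leave such detail to the full plan. For the Cox models this is a clarification, not a contradiction.

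**Conclusion.** The point holds as a modest efficiency improvement. The stated primary analysis does not use the factor by which the trial randomises. It remains valid and consistent with the sample size calculation. Under assumed site log-odds SDs of 0.2 to 0.5, it gives up about 0.2 to 1.2 points of power, with type I error of about 4.9% to 4.4%. At an extreme SD of 0.8 the loss is about 3 points. These sizes rest on assumed site shares and site effects. The direction needs only balance within site and some difference in event rates between sites.

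**What to change.** By a documented protocol amendment, decided without sight of outcomes by arm and before any unblinded analysis:

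- Make the primary analysis a two-sided Cochran-Mantel-Haenszel test stratified by study site at 5%, with the Mantel-Haenszel risk difference and its 95% confidence interval.
- Fix in advance a rule for pooling very small sites that depends on enrolment only, not on outcomes.
- Keep the Pearson chi-square with the crude risk difference as a sensitivity analysis.
- Apply the same stratified method to the components and the other binary outcomes that follow the primary method.
- State that the Cox models are stratified by site.

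The cost is a small amendment and the pooling rule. Wording in the analysis plan alone is not enough, because the published protocol names the primary test. No extra patients or data are needed, and the recruitment target stays at 2,278. On the article's status, 750 patients had been included, and the data safety monitoring board's safety analysis comes only after 1,000 have completed 30-day follow-up. An amendment at that stage would precede the first planned look at the data.

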### Sample Size Calculations and Statistical Analyses

#### Determination of Sample Size

Sample size was estimated based on our already completed observational multi-center study in 298 patients with profound hyponatremia (37, 38). The study showed a 30-day mortality rate of 6.4% and a 30-day rehospitalization rate of 18.5%. Of the re-hospitalized patients, ~2% died and thus were counted twice. We therefore propose a combined event rate of 23% under standard care. Our systematic review identified only one study that investigated the impact of targeted correction of hyponatremia on mortality and rehospitalization (25). In this observational study, an absolute reduction of the combined event rate of 7.1% (33.7 vs. 26.6%) was reported. Through our intervention, we expect to achieve an absolute risk reduction for mortality and rehospitalization of 5 %. Sample size was calculated for a Pearson's χ^2^-test. We set 80% power for a two- sided test with an α error of 5%. A drop-out rate of 10% was assumed. In order to have 2050 evaluable patients, 2,278 patients must be recruited.

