## Discussion

The current study protocol presents the design for a randomized controlled trial to study whether targeted treatment of hyponatremia reduces the risk of mortality and rehospitalization associated with hyponatremia. This trial is conducted in different European hospitals, including non-academic centers ensuring generalizable data is produced. In addition, adult patients with hypovolemic, euvolemic and hypervolemic hyponatremia will be included allowing for a broad representation of hyponatremic patients.

Assessing the contributory effect of hyponatremia on mortality is difficult (21), as patients presenting with hyponatremia often have severe and complex underlying conditions (39). A recent large retrospective study (*n* = 94,352) attempted to minimize the influence of confounding by optimizing comparability through propensity-score matching of hyponatremic with non-hyponatremic patients (40). Hyponatremia was indeed associated with increased risk of short-term adverse events including in-hospital mortality. Interestingly, the increased risk of in-hospital mortality did not apply to patients with hyponatremia secondary to SIAD. In a previous study designed to evaluate mortality risk specifically associated with SIAD, mortality rates were lower in patients with SIAD compared to patients with hyper- or hypovolemic hyponatremia. However, mortality rates in SIAD were still higher compared with normonatriemic patients (41).

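### The primary analysis is crude although age, sex, baseline sodium and underlying disease are collected: a valid test, but it leaves a modest amount of precision unused

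*Protocol article*

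**What the plan says.** Protocol article, Primary Analysis: for the 30-day composite of death or rehospitalisation, "the Pearson's χ^2^-test without Yates's correction will be applied", and "The estimated absolute difference between study arms will be reported alongside its 95% confidence interval". No covariate is named. Under Secondary Analysis, each component is analysed in the same way, and the Cox models have trial arm as their explanatory variable.

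Determination of Sample Size plans for this same test: "We therefore propose a combined event rate of 23% under standard care"; "we expect to achieve an absolute risk reduction for mortality and rehospitalization of 5" percentage points; "We set 80% power for a two- sided test with an α error of 5" per cent; "A drop-out rate of 10% was assumed". The result is 2,050 evaluable and 2,278 recruited patients.

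Randomization is stratified by study site only. Subgroup Analyses uses sex, age, severity of hyponatremia and "underlying disease (stroke, heart failure, SIAD, hepatic impairment, chronic kidney disease, malignancy, surgical diagnosis", together with the main treatment used. The trial must therefore collect all of these.

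On prognosis, the Background says that underlying and concomitant disease may contribute to the excess mortality. The Discussion says that "patients presenting with hyponatremia often have severe and complex underlying conditions". It also reports higher mortality with malignant but not with non-malignant SIAD, and lower mortality with more severe hyponatremia.

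**The concern.** A crude difference in proportions discards what baseline variables tell us about a patient's risk. When such variables are collected anyway, standardising over them gives an estimate of the same marginal risk difference with smaller variance, at the same error rate and sample size. It also corrects for chance imbalance in, say, malignancy. Stratifying by site does not balance these patient-level factors.

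The planned power has no margin above 80%. The Discussion itself expects reduced adherence, early discharge before full correction and possibly better hyponatremia management in the control group, and each of these would shrink the observed effect. It also says that a null result would lead hyponatremia to be seen more as a marker of disease severity than as a cause. A false negative would therefore be costly.

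**Working it through.** **Inputs from the article.** Control risk 0.23; intervention risk 0.23 − 0.05 = 0.18; two-sided α 0.05; power 0.80; 2,050 evaluable patients, so 1,025 per arm; drop-out 10%.

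**Input that the article does not give.** R², the share of outcome variance explained by the baseline covariates. I assume 0.02 to 0.15.

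**Step 1: reproduce the plan.** The mean risk is 0.205.

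n per arm = [1.96·√(2·0.205·0.795) + 0.8416·√(0.23·0.77 + 0.18·0.82)]² / 0.05² = [1.119 + 0.480]² / 0.0025 ≈ 1,023.

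The total is 2,046, against 2,050 stated. Recruitment is 2,050 / 0.9 = 2,278, as stated.

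Power at 1,025 per arm = Φ[(0.05·√1025 − 1.119) / 0.570] = Φ(0.846) = 80.1%.

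The 95% CI half-width is 1.96·√(0.3247 / 1025) = 3.49 points.

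**Step 2: power with adjustment.** The variance of the risk difference is multiplied by about (1 − R²), so 1,025 is replaced by 1,025 / (1 − R²). Example for R² = 0.10: 1,025 / 0.90 = 1,139 and Φ[(0.05·√1139 − 1.119) / 0.570] = Φ(0.997) = 84.1%.

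| Assumed R² | Power at 2,050 | Evaluable N for 80% power | CI half-width (points) |
|---|---|---|---|
| 0 (crude) | 80.1% | 2,046 | 3.49 |
| 0.02 | 80.9% | 2,006 | 3.45 |
| 0.05 | 82.1% | 1,944 | 3.40 |
| 0.10 | 84.1% | 1,842 | 3.31 |
| 0.15 | 86.1% | 1,740 | 3.22 |

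**Step 3: check by simulation.** Each scenario had 4,000 trials of 2,050 patients, with one normally distributed risk score on the logit scale. The adjusted analysis was a logistic model standardised to a marginal risk difference, with an influence-function standard error.

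| Score SD | R² (AUC) | Crude power | Adjusted power | Adjusted type I error |
|---|---|---|---|---|
| 0.36 | 0.02 (0.60) | 79.9% | 81.2% | 5.1% |
| 0.75 | 0.08 (0.69) | 80.2% | 83.3% | 4.8% |
| 0.95 | 0.12 (0.74) | 80.2% | 85.2% | 5.3% |

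The simulation standard error of a 5% error rate is √(0.05·0.95 / 4000) = 0.3 points, so the error rates are consistent with 5%. The simulated model was correctly specified and had no site terms, so it checks the formula and does not predict this trial's gain.

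**Step 4: where R² is likely to lie.** The article's planning rates are 18.5% rehospitalisation and 6.4% death, with about 2% counted twice: 18.5 + 6.4 − 2 = 22.9%. Most events are rehospitalisations, while the article's statements on prognosis concern mortality. The lower rows of R² are therefore as credible as the upper ones.

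**The case against.** The strongest reply is that nothing is broken. Under randomisation the chi-square test and crude difference are valid. They answer the stated objective and match the sample-size calculation, which reproduces. A condensed article may also leave adjusted analyses to a statistical analysis plan that is not shown. All of this stands, and it limits the point to efficiency. It does not remove the point, because the article positively names the crude analysis as primary, and an adjusted sensitivity analysis elsewhere would leave that unchanged.

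Three stronger readings are tempting, and the documents do not support them.

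- A reader might infer that the trial regards these factors as the main drivers of outcome. It does not say so. The Background speaks of a possible combination of causes and an open debate, age appears only as a subgroup cut, and the relation with sodium severity is called paradoxical. That relation is inverse, but this does not matter for adjustment.
- A reader might infer a large loss of power. No R² or AUC is given, and at R² = 0.02 the gain is less than one point.
- A reader might call the 5-point effect optimistic. The only comparable effect cited is 7.1 points, and the trial planned for less.

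One practical objection also stands. The article does not say when the underlying diseases are recorded. The final hyponatremia diagnosis is made at discharge, and in the control group the diagnostic work-up is left to the attending physician. Only values fixed before randomisation can be used.

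**Conclusion.** The point holds as unused precision. For the same marginal 30-day risk difference, adjustment would raise power at 2,050 evaluable patients from 80.1% to between 80.9% and 86.1%, a gain of about 1 to 6 points. The CI half-width would fall from 3.49 to between 3.45 and 3.22 points. The range rests wholly on the assumed R² of 0.02 to 0.15, and the lower part is plausible for a composite made up mostly of rehospitalisations. It also takes the planning rates of 23% and 18% as true. The change is worth making because the data are needed anyway and the design has no spare power, but the stated analysis would not give a wrong answer without it.

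**What to change.** Before unblinding, that is before anyone who decides on the analysis has seen outcomes by arm, amend Primary Analysis as follows.

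- **Primary estimate and test:** the marginal 30-day risk difference, standardised (g-computation) from a logistic model, with a robust standard error and 95% CI.
- **Model terms:** arm; site, as the stratification factor; age and baseline sodium as continuous variables; sex; malignancy; heart failure; chronic kidney disease; hepatic impairment. The four diseases are the listed ones that the Background or Discussion mentions in connection with prognosis. Confirm that each is recorded before randomisation, and drop any that is not.
- **Excluded:** SIAD or any other final aetiology, and the main treatment used. These are determined after randomisation.
- **Supporting analysis:** the chi-square test and crude difference as now written.
- **Components:** death and rehospitalisation in the same way.

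The model is affordable for the composite. With the nine centres in the Ethics Statement it has 1 + 8 + 7 = 16 coefficients besides the intercept, against about 0.205 × 2,050 = 420 events, or 26 per coefficient. For death alone, at 6.4% in both arms, there would be about 131 events, or 8 per coefficient, so a rule for pooling small sites should be written in advance.

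The cost is an amendment of the stated primary analysis, a rule for missing covariates and some more programming. No further patients or visits are needed, and no further data as long as the listed factors are already recorded before randomisation.
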